### Randomization and blinding

The independent Karolinska Trial Alliance (KTA) has set up a randomization system on the website randomize.net, based on list randomization with even blocks of random sizes determined by KTA and not shared with the researchers. Research assistants, who are not involved in other aspects of the trial and have limited knowledge of the differences between the study arms, will conduct each individual randomization using this website. The platform ensures concealment and integrity by performing real-time allocation, revealing the treatment assignment only after participant enrollment, and maintaining a comprehensive audit trail with timestamps and user activity logs. To minimize placebo and nocebo effects, participants will remain blind to the availability of different treatment options in the study arms. They will be briefly informed that the PCC is evaluating two types of assessments, both more comprehensive than standard routine. As the PCBH arm also includes extensive pre-treatment questionnaires, which are not part of standard PCBH procedures at the PCCs, this design ensures that both study arms are perceived by participants as offering a more thorough assessment. However, participants will not be told which assessment they were allocated to, ensuring blinding to both the type of assessment and treatment options.

Given the prompt availability of PCBH PCCs, often providing same-day appointments, it is worth noting that participants in this study are randomized immediately upon identification, even before completing the pre-measure. The randomization result is noted in the clinician’s schedule, allowing them to conduct assessments in accordance with the randomization during the initial visit. However, only patients who consent to the study and fill in the pre-measure will be included in analyses.

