### Models of clinical assessment

#### Contextual assessment (Core PCBH arm)

Clinicians in PCBH place a significant importance on understanding the patient’s current context and their strategies for managing stressors and unwanted experiences. The therapist explores the patient’s life context using a semi-structured interview called the Contextual Interview (CI), focusing on finding what triggers the unwanted experiences, when and how often they occur, and the trajectory of the problem. The goal is to promote a person-centered, whole-person perspective, while collecting clinically relevant information (such as avoidance behaviors, life skill deficits and dysfunctional coping strategies) to facilitate individually tailored interventions. In this model, the CI is regarded as a therapeutic intervention in its own right as opposed to a way of merely collecting information, as it broadens the patient’s perspective, helping them see their symptoms and problems within a wider context [29]. This shift in perspective is thought to foster insights that may inspire new ideas or behaviors. As such, a collaborative effort to identify and introduce an intervention is made during the first visit, directly after the CI. While the initial assessment and first intervention are typically completed within a single half-hour visit, both the assessment process and intervention strategies can be further refined during subsequent patient visits if needed. In contrast to the diagnostic assessment described below, the clinician pays little attention to whether the patient fulfils the criteria for a psychiatric diagnosis. In this study, clinicians do however have access the answers of the pre-treatment questionnaires, including the result of the automated diagnostic screening algorithm, and choose freely if they use them. As the study is integrated into routine healthcare, patients requiring more specialized care will be referred to an appropriate level of care irrespective of their randomization assignment.

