#### Extended diagnostic assessment (Extended PCBH arm)

Manualized CBT operates within the medical model of psychiatry, which means that the aim of treatment is to achieve remission of an identified disorder or condition [1]. It is therefore seen as pertinent to assess which diagnosis a patient suffers from, so that the correct protocol can be chosen. The demands for a structured assessment are even greater in GSH, as the standardized self-help material limits the possibility for re-assessment, adaptions and individualization of content during treatment.

In this study, the diagnostic assessment consists of three parts: an automated algorithm described below (see Measures), based on patients’ pre-treatment self-ratings to screen for diagnoses and overall suitability for GSH, an interview focused on the patient’s medical history, symptoms and life context, and the use of selected parts of Mini-International Neuropsychiatric Interview (M.I.N.I.) [30] based on which problem areas the algorithm identified as relevant. The assessment takes place over two 30-minute visits. A key difference between the two types of assessment is that, in the diagnostic assessment, there is a clear distinction between assessment and intervention. The assessment is completed first, and only after that is a decision made about which interventions to proceed with at a subsequent visit. While some questions may naturally overlap (such as those regarding the life context), in this form of assessment, they are primarily seen as a means of gathering information rather than initiating an intervention.

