### Data analysis plan

Due to the pragmatic nature of the study, where randomization occurs early – after patients have been identified and invited to participate, but before they are formally included in the trial – there is an increased risk of randomized participants during assessment or treatment being deemed unsuitable for both GSH and BI due to a need for specialized or primarily medical treatment. These participants will be excluded from most analyses but are expected to be randomly distributed between study arms. Another consequence of the pragmatic design is that patients may complete the pre-treatment measures up to a week after their initial visit to manage the usually very brief waiting time in PCBH. This could particularly impact within-group BI effects, as treatment begins during the first visit. To address this, a sensitivity analysis excluding late responses will be conducted, along with an analysis of missing data to evaluate its potential impact.

Several comparisons will be made to address the research questions. For research questions (1) and (3), we will conduct between-group comparisons on primary and secondary measures at the care model level, specifically comparing all participants in PCBH group with those in the PCBH + GSH group. To address research question (2), we will compare the subgroup of patients who received GSH (the EXT-I-GSH group) within the PCBH + GSH model with those who were retrospectively assessed as indicated for structured treatment but were randomized to the core PCBH arm and therefore did not receive GSH (the CORE-I-BI group). For the subgroup analysis examining whether GSH has a greater impact on conditions where the protocol is expected to have more specific effects (insomnia, panic disorder, social phobia, health anxiety disorder, and OCD) compared to conditions the effects are expected to be more general and non-specific (depression, GAD, and stress), analyses will evaluate whether patients in the former group show larger differences between GSH and BI than patients in the latter group. Research question (4) will be analyzed at both the care model and treatment type levels, as factors such as patient satisfaction, treatment content, patient behavior, and adverse events may be influenced by both the assessment and treatment strategies.

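### Patients found after randomisation to need other care are excluded from most analyses on an unsupported expectation of balance, and it is unclear whether the primary comparison is affected

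*Protocol article*

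**What the plan says.** The Data analysis plan section anticipates "randomized participants during assessment or treatment being deemed unsuitable for both GSH and BI due to a need for specialized or primarily medical treatment". It then sets the rule: "These participants will be excluded from most analyses but are expected to be randomly distributed between study arms". It does not list which analyses are meant. The next paragraph defines the comparison for research questions 1 and 3 as "specifically comparing all participants in PCBH group with those in the PCBH + GSH group". The sensitivity analysis named there leaves out late baseline responses, and an analysis of missing data is added; neither addresses the excluded patients.

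Under Randomization and blinding, the analysed set is limited to patients who consent and complete the pre-measure. On who knows the arm, the section says: "The randomization result is noted in the clinician’s schedule, allowing them to conduct assessments in accordance with the randomization during the initial visit". The blinding it describes is that of participants: "participants will remain blind to the availability of different treatment options in the study arms".

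The assessments differ by arm. In the core arm, "the clinician pays little attention to whether the patient fulfils the criteria for a psychiatric diagnosis", and use of the algorithm result is optional. In the extended arm, "The assessment takes place over two 30-minute visits", with a history and symptom interview, selected M.I.N.I. parts and required use of the algorithm.

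**The concern.** Exclusions after randomisation are harmless only if they are unrelated to arm, both in number and in the prognosis of those removed. Here the event that triggers exclusion lies downstream of the allocation. Patients are randomised between care models, and assessment is the first thing in which those models differ. A longer, more diagnostic work-up may uncover a need for other care more often, or in a different kind of patient, than a brief contextual interview. Exclusion can also arise during treatment, once the arms have diverged further. Nothing in the article suggests that the person making the judgement is unaware of the arm.

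If such patients leave the primary analysis, the remaining groups are no longer those that randomisation formed. Referral elsewhere is also a consequence of the care model, and question 1 is asked at the level of the care model. The planned effect is small (d = 0.20) and the non-inferiority margin is equal to it, so a modest selection effect could matter for either conclusion.

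**Working it through.** **1. The plan's own sample sizes (Power analysis section).**
- Superiority, d = 0.20, two-sided alpha 0.05, power 80%: n per arm = 2 × (1.960 + 0.842)² / 0.20² = 392.4, so 393; total 786; 786 / 0.80 = 982.5, so 983. This reproduces.
- Non-inferiority, margin 0.20, one-sided alpha 0.05, power 80%: 2 × (1.645 + 0.842)² / 0.20² = 309.1, so 310; total 620; 620 / 0.80 = 775. This reproduces.

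The sample size is not in error. The point concerns who is analysed.

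**2. Which population the text defines.** One sentence removes referred patients from most analyses; the next paragraph compares all participants by arm for questions 1 and 3. Tables 1 and 3 contain only groups that received BI or GSH, so a patient who received neither has no group. Exclusion from the primary analysis is therefore plausible but not stated.

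**3. Possible bias if the exclusion applies to question 1.** The documents give no exclusion rates and no prognosis for excluded patients, so these inputs are assumptions:
- e_core and e_ext: proportion excluded in each arm.
- D: how much worse excluded patients would score at FU12 than retained ones, in SD, taken as equal in both arms.

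With no true effect and equal means before exclusion, each arm's retained mean shifts by e × D, so spurious d = (e_ext − e_core) × D. Two-sided type I error uses SE = √(2/393) = 0.0713.

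| Core vs extended excluded | D | Spurious d | Share of 0.20 | Type I error |
|---|---|---|---|---|
| 5% vs 5% | any | 0 | 0 | 5.0% |
| 5% vs 8% | 0.5 to 1.0 | 0.015 to 0.03 | 7% to 15% | 5.5% to 7.0% |
| 5% vs 10% | 0.5 to 1.0 | 0.025 to 0.05 | 12% to 25% | 6.4% to 10.8% |
| 5% vs 15% | 0.5 to 1.0 | 0.05 to 0.10 | 25% to 50% | 10.8% to 28.9% |

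Swapping the arms reverses the sign. Equal rates are not sufficient for balance: at 5% excluded in both arms, a difference of 0.3 to 0.5 SD in the severity of those excluded gives 0.05 × 0.3 = 0.015 to 0.05 × 0.5 = 0.025.

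**4. Power, if 983 is counted before these exclusions.** With 5% excluded and 20% of the rest missing: 983 × 0.95 × 0.80 = 747 analysable, 373.5 per arm. Power = Φ(0.20 / √(2/373.5) − 1.960) = Φ(0.773) = 78%. Exclusions of 10% and 15% give 76% and 73%.

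**The case against.** The defence has substance.

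- **The primary analysis may be untouched.** Most analyses does not mean all, and the section then says all participants for questions 1 and 3. Questions 2, 5 and much of 6 need patients who received BI or GSH, and the exclusion may be meant for those. A reader might infer that the primary comparison is definitely non-randomised; the text does not establish that. What stands is that the section does not settle it.
- **Detection may differ less than it appears.** Both assessment sections say that patients needing specialised care are referred, the core section explicitly whatever the arm. Core clinicians can see the same questionnaires and algorithm result and can refine the assessment at later visits. The M.I.N.I. parts follow the problem areas the algorithm flags, so they serve fit to GSH more than a general search for other needs. Extended-arm clinicians may bypass the diagnostic work-up when GSH is clearly unsuitable. All this narrows the difference. It does not remove it: a common referral policy governs what follows once need is recognised, not how often it is recognised, and core clinicians need not use the algorithm.
- **Direction is not known.** It is tempting to say that the more thorough arm sheds more poor-prognosis patients and so looks better. The documents do not show this. Patients caught only by a longer assessment may be milder, and the difference could run the other way.
- **The power loss is conditional.** The Power analysis section says recruitment continues until the power target is reached, and does not say whether 983 is counted before or after these exclusions.

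**Conclusion.** The concern holds in this form: the plan excludes patients on a judgement made after randomisation, offers no support for expecting balance, and leaves the primary population contradictory or ambiguous. That the treating clinician makes the judgement is an inference from the assessment sections, though a strong one.

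The size is not known. Under the assumed ranges the spurious d is 0.015 to 0.10 in either direction, and it is nil if rates and severity match. An error favouring the extended arm would inflate superiority and make non-inferiority of core harder to show; the reverse would hide superiority and ease the non-inferiority claim. The fall to about 78% power holds only if 983 is counted before exclusions and 5% are excluded on top of the missing data. The documents do not support a claim that the trial is underpowered or that a bias of any particular size exists. The point still needs correcting before analysis, because it bears on the primary comparison and can be settled by a clear definition.

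**What to change.** - For questions 1 and 3, define the primary population as every consenting patient with a completed pre-measure, analysed in the arm randomised, including those later referred elsewhere. Use their follow-up data where collected and the planned multiple imputation otherwise.
- Make the exclusion of referred patients a sensitivity analysis, and list the other analyses to which it applies.
- Report both populations for the non-inferiority test. Including patients who received neither treatment can pull the arms together and favour a non-inferiority conclusion, so neither population is sufficient alone.
- Report the number excluded by arm, with reason and timing.
- Delete the clause expecting random distribution between arms.
- State whether 983 is counted before or after these exclusions.

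The cost is mainly wording, and the article says it was written before analyses start. The effect will be slightly diluted. The article does not say whether follow-up continued after referral; if it stopped, more outcomes must be imputed, and that should be reported.

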This means that patients are not randomized between treatments, but between models of care (PCBH vs. PCBH + GSH). In the extended arm (PCBH + GSH), patients will receive either GSH or BI based on their assessed suitability for GSH treatment. Suitability in this context means that the patient is both interested in and capable of engaging in a self-help treatment and has a primary problem related to mood, anxiety, stress-related conditions, or insomnia. In contrast, the core PCBH arm will include only patients who have received BI. However, within this group, there will be patients would have been suitable for GSH if it was available to them. After data collection is complete, these patients will be retrospectively identified using a standardized procedure that as closely as possible mirrors the extended assessment in the PCBH + GSH model. This approach will allow us to address the secondary research question [2] regarding the subgroup of patients suitable for GSH. The retrospective assessment can determine whether the patient’s primary problem falls within the specified categories and identify any clear indications that they would not be capable of engaging in treatment. However, patient preferences remain unknown, as they were never offered the option. Refer to Table 1 for an overview of the patient groups, along with the codes used to identify them.

**Table 1 Tab1:** Patient groups by randomization, indication for structured interventions, and treatment given

Model of care	Indicated for a structured intervention	Treatment received	Code
**Core PCBH**	Indicated	BI	CORE-I-BI^1^
	Not indicated	BI	CORE-N-BI^2^
**Extended PCBH**	Indicated	GSH	EXT-I-GSH^3^
	Not indicated	BI	EXT–N-BI^4^

^1^Retrospectively indicated for a structured intervention for mood, anxiety, stress-related conditions, or insomnia but received brief interventions (BI)

^2^Retrospectively not indicated for a structured intervention and received brief interventions (BI)

^3^ Assessed by the clinician as indicated for a structured intervention and received guided self-help (GSH)

^4^ Assessed by the clinician as not indicated for a structured intervention and received brief interventions (BI)

Note: In the Core PCBH arm, indication for a structured intervention is assessed retrospectively by an expert rater. In the Extended PCBH arm, indication is assessed in real-time by the regular care clinician

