The clinician is instructed to always use the results of the automated algorithm to inform the focus of the M.I.N.I. interview. As the GSH treatments in this study are possible to use with subclinical problems, the goal of the assessment is not necessarily for the patient to meet a specific diagnosis but rather to pinpoint the problem area most relevant to the patient’s concerns. The diagnostic evaluation concludes with the clinician providing feedback to the patient regarding the assessment results and, when appropriate, offering GSH for the identified condition. If GSH is not a good fit or the patient declines the treatment, they are offered BI. In such cases, BI may be initiated during the first visit if time permits or is otherwise scheduled for a follow-up appointment. Clinicians may also bypass the diagnostic assessment and proceed directly with BI if it is clear from the outset that the patient is unsuitable for GSH. Examples of this are if the patient’s primary concern clearly falls outside the issues addressed by the GSH materials used in this study (for example substance abuse). As in the contextual assessment, patients requiring specialized care will be referred accordingly.

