#### Retrospective algorithm for assessing indication for structured treatment

To address research question (2) – which examines whether patients who would have been suitable for GSH but did not receive it face a risk of undertreatment – we have developed an assessment model to retrospectively evaluate patients’ indications for structured treatment related to mood disorders, anxiety, stress-related conditions, or insomnia among those randomized to the core PCBH model. The assessment model is designed to mirror the clinicians’ extended, diagnostic assessment as closely as possible, with the crucial distinction that categorization is based solely on self- and clinician-reported data, and patient treatment preferences are unknown since they are never offered the possibility to receive GSH. Patients in the core PCBH arm who are retrospectively assessed as not indicated for structured treatment are assigned to the CORE-N-BI group, while those who meet the criteria are placed in the CORE-I-BI group. The same retrospective assessment will be conducted for patients in the extended PCBH arm to allow for comparisons between the retrospective and real-life assessments; however, this will not impact their group assignment.

The retrospective assessment consists of four steps:

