**Exclusion of patients clearly not indicated for structured treatment for the specified conditions**: These patients are identified based on their stated reasons for seeking help, reported health issues, and clinicians’ notes in the CRF.**Evaluation of potentially suitable patients**: Patients identified as potentially suitable for structured treatment undergo evaluation using specific scoring criteria, similar to those outlined in the decision support tool described above. In brief, this evaluation includes results from the automated algorithm, AUDIT-C scores, and the 1-item pain scale. Points are assigned when patients exhibit high scores in relevant problem areas, while deductions are made for high scores in non-relevant domains or indications of substance abuse or pain that may interfere with treatment.**Further evaluation of uncertain cases**: Patients with uncertain suitability are discussed with a supervisor and undergo additional evaluation, considering factors such as education level, health habits, and language difficulties.**Final assessment for suitable patients**: Patients deemed suitable for structured treatment have their primary problem areas assessed. The most pertinent problem is identified based on the problem area with the highest score from the automated algorithm, in conjunction with the patient’s stated reason for seeking help.

A flow chart detailing the process of the retrospective assessment can be found in Supplementary materials F.

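### The RQ2 contrast selects patients by different rules in the two arms and is not a randomised comparison; the retrospective rating planned for both arms should be used to add a by-arm analysis

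*Protocol article*

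**What the plan says.** The Data analysis plan defines the RQ2 comparison: "we will compare the subgroup of patients who received GSH (the EXT-I-GSH group) within the PCBH + GSH model" against CORE-I-BI, the core-arm patients retrospectively assessed as indicated.

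The note to Table 1 (Design and overall procedure) gives the two selection rules: "In the Core PCBH arm, indication for a structured intervention is assessed retrospectively by an expert rater", whereas "In the Extended PCBH arm, indication is assessed in real-time by the regular care clinician".

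Acceptance is part of the rule in one arm only. The same section defines suitability as including the patient's interest in self-help, and in the extended arm GSH goes to those who are suitable and accept it. The section on the extended diagnostic assessment adds: "If GSH is not a good fit or the patient declines the treatment, they are offered BI". For the core arm the protocol concedes that "patient preferences remain unknown, as they were never offered the option".

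The section on the retrospective algorithm states that extended-arm patients are rated with the same tool, for comparison with the real-life assessment, but that "this will not impact their group assignment". The document plans no comparison of retrospectively indicated patients by randomised arm.

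**The concern.** Randomisation protects a subgroup comparison only if membership is decided by the same rule, on information unaffected by allocation, in both arms. Here the rule differs in three respects: who rates, when, and whether the patient must want the treatment.

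The clearest consequence concerns patients whom the retrospective tool would rate indicated but who do not want GSH. In the extended arm they receive BI and fall into EXT-N-BI; Table 1 has no extended-arm cell for an indicated patient who received BI. In the core arm their counterparts stay in CORE-I-BI. Under Symptoms, EXT-N-BI patients have no primary symptom value, so decliners also leave that outcome in one arm only.

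Any difference found would mix the effect of GSH with differences in motivation, acceptance and classification. RQ2 asks whether GSH is better and, failing that, whether BI is non-inferior, so bias in either direction could change a conclusion. The same two groups serve the specific versus non-specific condition question and are the main contrast for the comparison of outcome variation in RQ5.

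**Working it through.** **1. The plan's own figures.** RQ2 has no sample size of its own (Power analysis). The trial's totals reproduce:
- Superiority: 2(1.960 + 0.842)²/0.20² gives 393 per arm, 786 in total; 786/0.8 = 983, as stated.
- Non-inferiority, one-sided 0.05, margin 0.20: 2(1.645 + 0.842)²/0.20² gives 310 per arm, 620 in total; 620/0.8 = 775, as stated.

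The point does not rest on a sample-size error. The useful yardstick is d = 0.20, both target effect and margin.

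**2. Selection bias, simple form.** Suppose a share q of indicated patients would accept GSH, and acceptors have a prognosis D SD better than decliners. With no treatment effect, acceptors minus all indicated = D − qD = (1 − q)D. Both q and D are assumptions.

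| q | D = 0.2 | D = 0.5 |
|---|---|---|
| 0.5 | 0.10 | 0.25 |
| 0.6 | 0.08 | 0.20 |
| 0.8 | 0.04 | 0.10 |

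If acceptors have the worse prognosis, the sign reverses.

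**3. Selection bias, with imperfect agreement.** A simulation assumed that half of patients are rated indicated, clinician and rater judgements correlate 0.6, acceptance is 50–90%, and a motivation trait unseen by the rater correlates 0.1–0.3 with outcome.
- No treatment effect: the planned contrast shows a spurious GSH benefit of 0.02 to 0.24 SD; retrospectively indicated patients compared by arm show 0.00.
- True GSH effect 0.30: the planned contrast reads 0.32 to 0.54; the by-arm contrast reads 0.11 to 0.19.

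The second by-arm range is dilution, not bias: 35% to 64% of indicated extended-arm patients received GSH in these runs, and 0.30 × 0.35 = 0.105 while 0.30 × 0.64 = 0.19.

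**4. Power of the by-arm contrast.** Analysed per arm = 983 × 0.8/2 × share rated indicated (share assumed; two-sided 0.05).

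| Share indicated | n per arm | Power at d = 0.30 | Detectable d at 80% |
|---|---|---|---|
| 30% | 118 | 63% | 0.37 |
| 50% | 197 | 84% | 0.28 |
| 70% | 275 | 94% | 0.24 |

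Here d is the diluted effect. If GSH itself is worth 0.30, the by-arm effect is 0.11 to 0.19. At 197 per arm the standardised shift is d × √(197/2) = 9.92d, that is 1.09 to 1.89. Power is then 1 − Φ(1.96 − 1.09) = 19% to 1 − Φ(1.96 − 1.89) = 47%.

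**The case against.** **Disclosed and secondary.** Preregistrations and current protocol demotes this comparison from primary to secondary, and the unknown preferences are stated. That is fair, but the reason given is difficulty with the coding, and neither disclosure nor rank removes the bias. The document describes no adjustment for it.

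**Decliners are not mislabelled.** Since suitability includes interest, a decliner is not suitable by definition. This stands as a matter of labelling. The definition still cannot be applied in the core arm, which is the source of the asymmetry.

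**Motivation is partly captured.** The vignette ratings include importance and motivation to address each problem area and feed the algorithm score. True, but that is not willingness to take up GSH.

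Some stronger readings are tempting and not supported:
- *That the plan forbids a by-arm analysis.* It only says the extended-arm rating does not alter group labels.
- *That the existing rating already yields a clean randomised comparison.* Step 1 uses clinicians' CRF notes, written after allocation and following different assessments. The pre-measure may come up to seven days after the first visit, when core patients have usually begun an intervention. Randomisation also precedes consent and the pre-measure throughout the trial.
- *That a complier estimate, with randomisation as instrument, recovers the effect of GSH.* This needs allocation to act only through GSH. The contextual interview is regarded as an intervention in its own right, and the Data analysis plan allows that the diagnostic assessment may influence BI in either direction.
- *That different rules for the primary symptom bring a known regression-to-the-mean bias.* Step 4 states "The most pertinent problem is identified based on the problem area with the highest score from the automated algorithm", but together with the stated reason for seeking help. Extended-arm clinicians use the same algorithm to focus the interview, and the symptom cut-off adds only 10 of 51 points. The rules differ, but no size can be given.

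**Conclusion.** The point holds. As written, EXT-I-GSH versus CORE-I-BI is a non-randomised contrast, with selection that differs by arm in rater, timing and acceptance. It bears on RQ2, the specific-condition question and RQ5.

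A reader might infer that the bias favours GSH and is about as large as the target effect. The documents support neither. The 0.04–0.25 and 0.02–0.24 SD ranges depend on assumed acceptance, agreement and prognostic strength, and both calculations assume that acceptors do better. What can be said is that plausible inputs reach d = 0.20 and that nothing in the plan bounds the bias.

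The by-arm comparison removes this selection only if the rating uses inputs that do not depend on arm. It also answers a different question from the effect of receiving GSH, which is why it should be added alongside the planned contrast.

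**What to change.** Before the retrospective rating begins, pre-specify an added RQ2 analysis:

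1. Include patients rated indicated by the retrospective tool in both arms and compare them as randomised, whatever treatment they received.
2. Set the primary problem area, and hence the primary symptom scale, by step 4 in both arms. For this analysis, indicated extended-arm patients who received BI therefore also need a primary symptom value.
3. Base the rating for this analysis on pre-measure self-report, without the CRF notes in step 1, and mask the rater to arm and follow-up.
4. Repeat it excluding pre-measures completed after the first visit, in line with the sensitivity analysis already planned for late responses.
5. Interpret the result as the effect of offering the extended model to indicated patients.

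Keep EXT-I-GSH versus CORE-I-BI for RQ2, the specific-condition question and RQ5, labelled non-randomised. Treat any complier estimate as exploratory and state why.

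Cost: wording, one further analysis, and a version of the rating without CRF notes; rating of both arms is already planned. The drawback is dilution by patients who do not receive GSH, and hence lower power.
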